### Study procedures and variables

#### Procedures and timeline

Entire schedule requires 30-months overall: 6-months (month1–6) for administration/ethics/field preparedness, 6-months (Month 7–12) for enrolment of participants until complete sampling, 12-months monitoring (Month 7–24) for complete follow-up of one-year, and 6-months (Month 25–30) for closing study sites, data processing, and reporting. During enrolment (M0) at the clinic, study clinicians will obtain informed consent and participant assent from legal guardian and the ADLHIV, respectively, followed by collection of socio-demographic, clinical and economic data, HIV history (including date of HIV diagnosis and WHO-clinical staging), complete history of ARV (ART and/or PMTCT, previous viral load and CD4/CD8 whenever available), as well as adherence levels. Intravenous blood (6 ml) will be collected from each ADLHIV for laboratory analyses at the CIRCB. Practically, CD4/CD8 (cells/mm [3] and percentage) and plasma viral load (PVL) will be performed for all ADLHIV using flow cytometry and real-time polymerase chain reaction (PCR) respectively. Among those experiencing VF, RNA (from plasma) and DNA (from buffy coat) extracts, isolated using the QIAamp commercially available Viral RNA and DNA Mini Kit (QIAGEN), be will be used for PCR-amplification of the protease-reverse transcriptase (PR-RT) region of HIV-1. GRT will be performed on PR-RT amplicons using Sanger-sequencing, as previously described [43]. HIVDR-associated mutations will be interpreted using *Stanford HIVdb* algorithm [18, 35, 36, 43]. GRT results will then guide the selection of effective ARVs available in the national ART programme (first-, second-, and third-line regimens) and outcomes (WHO-clinical staging, viral and CD4/CD8 measurements) will be measured at 6 and 12 month-visits.

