#### Definition of study variables

VF will be defined as two consecutive PVL ≥ 1000 copies/ml within 1 month under intensive adherence counselling and support [10]. Participants with PVL ≥ 1000 copies/ml at any visit will therefore undergo adherence counselling and extra-visit after 1 month to confirm or infirm VF.Immunological failure will be defined as persistent CD4 < 100 cells/mm [3] during follow-up.Clinical failure will be defined as WHO clinical stage 3 or 4 events or death. Clinical management outside the study protocol will be done according to local national guidelines.HIVDR will be defined as the presence of any mutation, in the PR-RT regions of HIV-1, known to reduce the efficacy of NRTI, NNRTI or protease inhibitor, as per the *Stanford HIVdb* algorithm [18, 35, 36, 43].Good adherence will be defined as ≥95% compliance to ART (i.e. only one missing dose), measured by pill count and by self-reported, during the past 30 days.EWIs will be defined and their respective performance targets are provided below: [10, 3, 8]

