
At enrolment, midpoint and endpoint, prevalence of VF and HIVDR (with 95% Confidence Intervals) will be described globally, by geographical settings and by site. Associated factors will be evaluated using multivariate logistic regression, with an estimative approach for the unbiased effect of ART regimens (first versus second-line) and HIV-1 diversity (CRF02_AG versus non-CRF02-AG) [18]. In order to provide the highest level of evidence amongst ADLHIV experiencing VF versus those on virological success, ART response will be described through time to event data analysis and mixed models for the trajectory of CD4 count and viral load, based on adjustments of baseline confounders (duration of treatment, age, gender, orphan hood, site). The effect of DRMs (from plasma versus buffy coat) on ART response will be evaluated using multivariate survival models, either Cox or Fine&Gray in the presence of death as competing event. Characteristics of patients LTFU will be described and, if necessary, inverse probability weights will be used. Primary outcome is the proportion of VF; secondary outcome is the proportion of acquired-HIVDR, or deaths, evaluated according to study site (referral centres versus management units), HIV-1 subtype distribution (CRF02_AG versus non-CRF02-AG) [18], adherence levels (< 95% vs. ≥95%) [44], and ART regimens (first versus second-line) [35]. Proportion of adolescents with low-level viremia (≥400 or ≥ 50copies/ml) who finally end in VF will be described, along with HIVDR profile at endpoint [45]. We will build a multivariate logistic model with predictive approach to evaluate the association of socioeconomic conditions with adherence levels and HIVDR emergence [44, 46].

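### The baseline confounders named for the ART-response models leave out adherence at enrolment, so these estimates are open to confounding of unknown direction

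*Protocol article*

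**What the plan says.** All references are to the protocol article.

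- **Adjustment set.** Data collection and analysis describes ART response by "time to event data analysis and mixed models for the trajectory of CD4 count and viral load", contrasting participants "amongst ADLHIV experiencing VF versus those on virological success". The adjustment is stated as "based on adjustments of baseline confounders (duration of treatment, age, gender, orphan hood, site"). Nothing marks the list as a set of examples.
- **DRM model.** The next sentence of the same section reads "The effect of DRMs (from plasma versus buffy coat) on ART response will be evaluated using multivariate survival models", by Cox or, with death as a competing event, Fine and Gray. It names no covariates.
- **What is recorded at month 0.** Procedures and timeline has the clinicians collect "complete history of ARV (ART and/or PMTCT, previous viral load and CD4/CD8 whenever available), as well as adherence levels". It also states that CD4/CD8 and "plasma viral load (PVL) will be performed for all ADLHIV using flow cytometry and real-time polymerase chain reaction (PCR) respectively".
- **Adherence as a variable.** Definition of study variables states: "Good adherence will be defined as ≥95% compliance to ART", by pill count and self-report over the past 30 days.
- **Adherence elsewhere.** The Background lists poor adherence among the circumstances that raise the risk of resistance. Data collection and analysis compares outcomes by adherence below versus at or above 95%, and relates socioeconomic conditions to adherence in a separate logistic model. Neither use puts adherence into the ART-response models.

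**The concern.** In an observational cohort, a variable that influences both the factor under study and the later outcome has to be adjusted for. On the article's own account adherence is such a variable. Poor adherence is linked to resistance in the Background, and adherence support is required before virological failure (VF) is confirmed, which presumes that adherence affects viral load. A list that includes orphanhood and omits adherence therefore looks badly chosen for models meant to give the strongest evidence on response.

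At stake is the interpretation of the response estimates. If adherence differs between the groups compared, part of a difference caused by taking or not taking the drugs will be credited to whatever defines the groups. For the DRM analysis, whose plasma versus buffy coat results are meant to inform the design of drug combinations (Discussion, objective 3), the error could make resistance look less harmful or more harmful than it is. The primary outcome, the proportion with VF, is descriptive and is not affected.

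**Working it through.** **1. Size of the DRM subset.** The plan's sample-size chain reproduces: 174 / 0.90 = 193.3, taken as 194; 194 / 0.80 = 242.5, taken as 243; rounded up to 250. With the plan's 40% VF rate and 20% sequencing failure, the sequenced VF participants expected at month 0 number 250 × 0.40 × 0.80 = 80.

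**2. What omission of adherence could do to the DRM effect.** The documents give no association between adherence and DRMs, so the following inputs are assumptions: 40–60% good adherers; DRM prevalence 90–95% in one adherence group and 65–70% in the other; response 80–85% in good and 55–60% in poor adherers; no true DRM effect.

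*Direction A: poor adherers carry fewer DRMs.* Take 50% good adherers, DRMs in 95% (good) and 65% (poor), response 85% and 55%.
- DRM prevalence: 0.5 × 0.95 + 0.5 × 0.65 = 0.80.
- Good adherers among carriers: 0.475 / 0.80 = 59.4%. Among non-carriers: 0.025 / 0.20 = 12.5%.
- Response in carriers: 0.594 × 0.85 + 0.406 × 0.55 = 72.8%. In non-carriers: 0.125 × 0.85 + 0.875 × 0.55 = 58.75%.
- Crude odds ratio: (0.728 / 0.272) / (0.5875 / 0.4125) = 1.88.

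*Direction B: poor adherers carry more DRMs.* Same inputs, with the two DRM prevalences exchanged.
- Good adherers among carriers: 0.325 / 0.80 = 40.6%. Among non-carriers: 0.175 / 0.20 = 87.5%.
- Response: 67.2% in carriers and 81.25% in non-carriers.
- Crude odds ratio: (0.672 / 0.328) / (0.8125 / 0.1875) = 0.47.

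| Assumed direction | Crude odds ratio over the stated ranges (true value 1) |
|---|---|
| A: poor adherers carry fewer DRMs | 1.29 to 2.04 |
| B: poor adherers carry more DRMs | 0.46 to 0.75 |

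**3. A second check on other assumed inputs.** Let p1 and p0 be the proportions of poor adherers with and without DRMs, and RR the risk ratio of a poor outcome for poor adherence. Leaving adherence out multiplies the DRM risk ratio by [p1(RR − 1) + 1] / [p0(RR − 1) + 1].
- RR = 3, p1 = 0.6, p0 = 0.3: 2.2 / 1.6 = 1.38.
- RR = 3, p1 = 0.3, p0 = 0.6: 1.6 / 2.2 = 0.73.
- RR = 1.5, same two pairs: 1.3 / 1.15 = 1.13 and 1.15 / 1.3 = 0.88.

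**4. The same in a Cox model.** Simulation with n = 250, 400 replicates, true DRM hazard ratio 2.0, 40% poor adherers and a hazard ratio of 2 for poor adherence (all assumed):

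| DRM prevalence, poor / good adherers | HR without adherence | HR with adherence |
|---|---|---|
| 65% / 40% | 2.26 | 1.97 |
| 40% / 65% | 1.67 | 2.03 |

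In steps 2 to 4 the bias changes sign with the assumed association between adherence and DRMs. Nothing in the documents settles that association.

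**The case against.** **The list does not govern the DRM model.** This stands as a matter of text. The five variables belong to the sentence on time-to-event and mixed models, and the DRM sentence names none. A reader might infer that the DRM estimates are certainly confounded; the article supports only the conditional statement that they are exposed if the same set is used. An article may leave the DRM covariates to a fuller plan, so their absence is not the finding. The finding is the list that is stated.

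**The direction is unknown.** This also stands. A reader might infer that omitting adherence makes DRMs look harmless. That needs poor adherers to carry fewer DRMs, which is possible among participants with VF, but the Background points the other way. Adherence support before VF is confirmed may also weaken the association. An unknown sign does not remove the problem, because nobody could correct an unadjusted estimate afterwards.

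**Viral load and CD4 at month 0 are missing too.** A reader might infer that these are equal omissions. They are not. In the mixed models they are already outcome values, viral load defines the VF versus success contrast, and either may lie on the path from resistance to response. With about 80 sequenced participants, and about 16 without DRMs if 80% carry them (assumed), there is little room for extra terms.

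**Precision.** A reader might infer that the omission costs precision. In the simulation above, adjusting for adherence did not lower the standard error of the log hazard ratio (0.181 to 0.186 and 0.180 to 0.187 in the two rows). Any power gain from adding viral load depends wholly on an assumed hazard ratio for it.

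**Adherence is used elsewhere.** True, but comparing outcomes by adherence level does not adjust the response models for it.

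**Conclusion.** The point holds for adherence. The article commits to a specific adjustment set for the ART-response models and leaves out a variable that it records at enrolment and itself links to resistance and outcome. The estimates are open to confounding, and the documents do not show that they are confounded to any given degree.

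The size is illustrative. On the assumed inputs with no true DRM effect, the crude odds ratio runs from about 0.5 to about 2.0. The simpler multiplier runs from 0.73 to 1.38. Both ranges rest on assumed links of adherence with DRMs and with outcome, and the first treats adherence as the only confounder and as measured without error. For DRMs, the conclusion also depends on the same five variables being used in that model.

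This is a worthwhile, inexpensive correction to secondary analyses. It does not touch the primary proportion.

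**What to change.** In Data collection and analysis:

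- Add month-0 adherence (below 95% versus 95% or more, as already defined) to the named set, giving duration of treatment, age, gender, orphanhood, site and adherence.
- State that the Cox or Fine and Gray model for DRMs uses the same set, with adherence taken at the failure visit for participants whose VF is first confirmed at month 6 or later.
- Keep month-0 viral load and CD4 out of the mixed models as covariates. In the time-to-event models, use them at most in a sensitivity analysis.

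The cost is a sentence or two and one more degree of freedom in a subset of about 80; the data are already collected. Pill count and self-report over 30 days are an imperfect measure of the adherence history that produced resistance, so some confounding may remain and should be acknowledged when the results are reported.

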## Discussion

Our research objectives will help in generating evidence for optimal monitoring and management of adolescents treated with antiretroviral therapy (ART) in a sub-Saharan African (SSA) context. Specifically, study objective 1 will help in understanding the significance of treatment failure among adolescents living with HIV (ADLHIV) in a resource-limited setting (RLS), will provide relative time-estimates for treatment failure, and propose locally affordable measures to limit ART failure in ADLHIV; study objective 2 will provide the burden of drug resistance according to the national treatment guidelines, and would inform on the adequacy between detected mutations and the most potentially active second- or third-line drugs for ADLHIV in such RLS. This study objective is inform if the development of HIVDR are specific to the different local HIV-1 clades, for possible clinical considerations for a specific management of adolescents in the country; study objective 3 will inform on the potential compartmentalisation of HIVDR among adolescents, in order to design drug combinations that provide maximal efficacy in a long run; study objective 4 will identify both programmatic factors favouring HIVDR emergence among ADLHIV, among which events of ARV stock outs and the quality of dispensing practices. This same objective will also identify the level of adherence of ADLHIV to ART, among which non-observance, delay drug pick-up and lost to follow-up. Importantly, with the exception of settings where HIV-1 subtype C prevails (found mainly in Southern Africa), our study impacts could be generalizable to the population of ADLHIV in several RLS, giving potential endorsements by national and international health regulatory bodies such the World Health Organisation (WHO) and UNAIDS.

## Data Availability

Not applicable.

## Abbreviations

ADLHIV: Adolescent living with HIV
AIDS: Acquired immunodeficiency syndrome
ART: Antiretroviral therapy
ARV: Antiretroviral
AZT: Zidovudine
BD: Becton Dickinson
CCR5: C-C chemokine receptor type 5
CD3: Cluster of differentiation 3
CD3: Cluster of differentiation 4
CD8: Cluster of differentiation 8
CIRCB: Chantal BIYA International Reference for research on HIV/AIDS prevention and management
CRF: Case reporting form
CRF: Circulating recombinant form
CXCR4: C-X-C motif chemokine receptor type 4
DNA: 2′-deoxy-ribose nucleic acid
DRM: Drug resistance mutation
EWI: Early warning indicators
FACS: Fluorescent activated cell sorting
GRT: genotypic resistance testing
HIV: Human immunodeficiency virus
HIVdb: HIV database
HIVDR: HIV drug resistance
IC: Interval confidence
ID: Identification
LPV/r: ritonavir-boosted lopinavir
LTFU: Lost to follow-up
M0: Month 0
M12: Month 12
M6: Month 6
NNRTI: Non-nucleoside reverse-transcriptase inhibitor
NRTI: Nucleoside reverse-transcriptase inhibitor
NVP: Nevirapine
PCR: Polymerase chain reaction
PMTCT: Prevention of mother-to-child transmission of HIV
PR-RT: Protease-reverse transcriptase
PVL: Plasma viral load
RLS: Resource-limited settings
RNA: Ribose nucleic acid
RT: Reverse transcriptase
RTI: Reverse transcriptase inhibitor
RTPCR: Reverse transcriptase polymerase chain reaction
SDC: Supplementary digital content
SSA: Sub-Saharan Africa
VF: Virological failure
WHO: World Health Organisation
